### Sample size

For our primary outcome, we aim to detect a reduction in inappropriate psychotropic drug prescribing of 5 points minimum (standard deviation = 15) on the APID index from the baseline to the final measurement (16 months) [23, 71]. We expect that APID values will be nested within NHs, the main level of randomization in our design. Assuming an average size of 25 residents per NH, a power of 0.80, a significance level (alpha) of 0.05, we will need 284 psychotropic drug users. Given the multilevel design with two measurements after baseline, we anticipate that we will then need to increase this to a sample size of 364 (15 clusters) for an intraclass correlation coefficient of 0.1 [44] and a calculated design factor of 1.28 (the factor at which the original N has to multiplied). To allow for a cluster dropout of about 10% [72], and to obtain an even number of clusters, we plan to include 16 clusters with 364 residents in total. Given that approximately 60% of residents with dementia will be prescribed psychotropic drugs [20], this number will need to be further increased to 607 residents. Previous studies have shown that we can also anticipate a loss to follow-up of about 30% per year [5], which would amount to 40% in the 16 months in our study. However, in the event a resident dies or moves away from the unit, we will enroll the newly admitted resident, precluding the need to account further for attrition. Consequently, the case mix during our study will vary, and information from dropouts will need to be included in an intention to treat analysis.

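### The 364 users (607 residents) contain no allowance for the 10% cluster dropout that the sample size section says they cover

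*Protocol article*

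**What the plan says.** All of this is in the protocol article, section Sample size.

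- The target is "a reduction in inappropriate psychotropic drug prescribing of 5 points minimum (standard deviation = 15) on the APID index", with "a power of 0.80" and "a significance level (alpha) of 0.05". This gives 284 psychotropic drug users before clustering.
- The cluster size enters as "Assuming an average size of 25 residents per NH". With an intraclass correlation of 0.1, the design factor is 1.28 and the requirement becomes "a sample size of 364 (15 clusters").
- The next sentence begins "To allow for a cluster dropout of about 10" per cent, adds the wish for an even number of clusters, and concludes "we plan to include 16 clusters with 364 residents in total".
- Because about 60% of residents use psychotropic drugs, 364 is then raised to 607 residents. Residents who die or move away are to be replaced by new admissions, so nothing more is added for individual attrition.

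**The concern.** The same total, 364, is given as the requirement before cluster dropout and as the figure that allows for it. It cannot be both. Only the cluster count changes, from 15 to 16, so the average number of users per home must fall.

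A reader of the section would conclude that the trial keeps 80% power if about one home in ten withdraws. If the total holds no reserve, power falls below target under the very loss the plan expects. Replacing residents does not help: it refills places in homes that stay in the trial and cannot replace a home that leaves.

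There is also a labelling problem. The 25 per home is called residents but enters a calculation whose unit is drug users. At 60% use, 25 residents would supply only 15 users (25 x 0.60).

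**Working it through.** **Inputs (Sample size section):** difference 5, SD 15, power 0.80, alpha 0.05 (two-sided reproduces the plan's figure), 25 per home, ICC 0.1, design factor 1.28, 60% users, about 10% cluster dropout. The allocation of 8 homes to each group is in Design and eligibility.

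**Step 1: reproduce the plan.**

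- Before clustering: 4 x [15 x (1.960 + 0.842)/5]² = 282.6, which is 142 per arm after rounding up, or 284.
- Stepped-wedge design factor with one baseline measurement, two steps, one measurement per step and n users per home: [1 + ICC(3n - 1)] / [1 + ICC(2n - 1)] x 3(1 - ICC)/[2(2 - 1/2)].
- At n = 25: (8.4/5.9) x 0.9 = 1.281, against the stated 1.28. The step and measurement settings are inferred from the described schedule and from this match.
- 284 x 1.28 = 363.5, so 364. 364/25 = 14.6, so 15 clusters. 364/0.60 = 606.7, so 607.

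Every stated figure reproduces, and none needs a dropout term.

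**Step 2: does the sixteenth home create a reserve?**

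- 364/16 = 22.75 users per home.
- Design factor at 22.75: (7.725/5.45) x 0.9 = 1.276.
- Users needed: 284 x 1.276, about 362, or 15.9 homes of 22.75. All 16 homes are needed.
- The abstract's target of 600 residents is 600 x 0.60 = 360 users, so it adds no margin either.

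**Step 3: power after losing homes.** Effective N = users/1.276, SE = 30/√(effective N), power = Φ(5/SE - 1.96).

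| Homes retained | Users | Effective N | SE | Power |
|---|---|---|---|---|
| 16, none lost | 364 | 285.3 | 1.776 | 0.804 |
| 15, one lost | 341.25 | 267.5 | 1.834 | 0.778 |
| 10% of users lost | 327.6 | 256.8 | 1.872 | 0.761 |
| 14, two lost | 318.5 | 249.7 | 1.899 | 0.750 |

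The 10% row corresponds to 14.4 homes and so lies between losing one home and losing two. Using the stated 1.28 directly gives 0.803, 0.777, 0.760 and 0.748, so the inferred settings hardly matter.

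**Step 4: what an allowance in the total would look like.** Sixteen homes at the assumed 25 users hold 16 x 25 = 400 users, or 400/0.60 = about 667 residents. A 10% loss leaves 360 users and power 0.798, which is close to target. The shortfall is therefore in the user total.

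**Step 5: per-home numbers.** 607/16 = 37.9 residents per home, of whom 22.75 would be users.

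**The case against.** The best defence is that going from 15 to 16 homes is the allowance. The unrounded requirement is 364/25 = 14.56 homes. 14.56 x 1.1 = 16.0 and 14.56/0.9 = 16.2, and the plan says only about 10%. At 25 users per home, losing one of 16 homes would leave 375 users and power 0.81. This stands as far as the number of homes goes. A reader might infer from 15/0.9 = 16.7 that 17 or 18 homes are needed, but that inflates a count already rounded up. The defence does not rescue the stated totals, because 364 and 607 were not raised with the homes.

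Second, the losses in the table are worst cases. The Data analysis section plans a multilevel model on repeated measurements, so a home that leaves after 8 months could still contribute its earlier data. Power would then lie between the tabulated value and 80%. This stands, and the restated figures should carry the assumption.

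Third, the loss is moderate: 2.6 points for one home, about 4 at 10% and about 5 for two. This also stands. It limits the consequence but does not make the sentence correct.

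That an article condenses a fuller protocol is no answer. The article states each step, and the steps conflict.

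**Conclusion.** Wrong as written. The 364 users and 607 residents are the requirement without cluster dropout, and the sentence presenting them as an allowance for it describes a reserve the numbers do not contain. By the plan's own method the chance of missing the target difference rises from about 20% with all homes retained to about 22% with one lost, 24% at 10% loss and 25% with two lost.

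These figures assume that a lost home contributes no data, that losses leave the two groups about equal, and that homes average 22.75 users.

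A reader might go further and infer that the trial misses 80% power even with every home retained, for example by applying a small-sample reference distribution to 16 clusters. The documents do not support that as part of this point. The plan specifies a Wald test, its own method gives 0.80 with no loss, and the choice of reference distribution is a separate question from cluster dropout.

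**What to change.** In the Sample size section:

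1. Delete the claim that 364 users (607 residents) allow for 10% cluster dropout. The wish for an even number of clusters can remain as the reason for 16.
2. State that, by the plan's method, 16 homes with 364 users give power of about 80% with no home lost, about 78% if one is lost, about 76% at 10% loss and about 75% if two are lost, assuming a lost home contributes no data.
3. In the cluster-size assumption, change residents to psychotropic drug users and keep the value 25. The step from 364 to 15 clusters depends on it.
4. Note separately that 364 users in 16 homes is about 23 users (38 residents) per home.

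The cost is a slightly less favourable stated power. No extra patients or homes are needed, and the design and analysis do not change.

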**Fig. 1 Fig1:**
[figure not shown]
RID study design. The randomization of nursing homes into start or deferred intervention groups. *Abbreviation: RID, Reducing Inappropriate psychotropic Drug use*

The study duration will be 16 months, split into two 8-month periods. Based on a pilot study, we estimated that the problem analysis for PAR-RCT would take about 2 months. We plan to allow 6 months to implement the chosen interventions because a longer period may lead to a loss of enthusiasm among NH staff, and because we anticipate high turnover rates among residents [5] and staff [32, 39]. The coaching will also be time and cost intensive, and the amount of data collected will require a huge investment from research assistants and NH staff.

Although we believe that 8 months will be optimal for these reasons, we do recognize that it might be insufficient to bring about a change in NH practice. Therefore, we plan to use the stepped-wedge design to compare the 8 month intervention with a 16 month extended intervention that will allow us to study possible long-term effects. Using a computer program, 16 NHs will be randomized by fixed-block randomization into an intervention group or a deferred intervention group (8 NHs each). In Period 1, the intervention group (Fig. 1, green blocks) will start by implementing the PAR method, while the deferred intervention group will start with care as usual. After 8 months, Period 2 will start, and the deferred intervention group will start the intervention and the original intervention group will complete a second intervention phase.

The primary outcome will be the reduction of inappropriate psychotropic drug prescribing based on data collected at baseline, 8 months, and 16 months. The statistician will be blinded to the cluster randomization process, and the NH staff and researchers will be aware of their participation group by design. Given that we aim to intervene at the DSCU level and that residents are not directly subject to an intervention, we have no discontinuing criteria, trial stopping rules, or modifying allocations.

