### Study population and recruitment

NHs will be recruited by organizing a national kick-off and using media channels to gain attention. Any interested NHs in the Netherlands can apply to participate and will be considered eligible if the board of directors and the client council agree to participate and are prepared to invest the requisite time. We will exclude NHs in which major organizational changes are expected during the study period or if other projects related to psychotropic drug use are currently running.

The study population will comprise residents with dementia who reside in psychogeriatric units (e.g., DSCUs). NHs can have several DSCUs, and several DSCUs from one NH can participate. However, DSCUs designed to deliver care for residents with Korsakov syndrome, acquired brain injury, Down syndrome, or young-onset dementia will be excluded. Although interventions will be aimed at the DSCU level, we will still need to gather data on residents to assess outcomes. Residents will be eligible to participate if they have a diagnosis of dementia according to the Diagnostic and Statistical Manual of Mental Disorders (fifth edition), have a life expectancy of at least 3 months, as judged by a physician, and provide written informed consent. We will also include users and nonusers of psychotropic drugs. It is anticipated that most residents will be at an advanced stage of dementia and may be mentally incompetent. The physician of the relevant DSCU will therefore be asked to assess a resident’s mental competence to provide informed consent. If they are not deemed competent, an employer of the registry office at each NH will send the informed consent form to a residents’ legal representative. In the absence of a response, a reminder request to return the informed consent form will be made once. If no response will be obtained, residents will not be included.

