^c^The EBPAS + organization culture questionnaires are administered in the context of the problem assessment at 0 months (start intervention group) or 8 months (start deferred intervention group), as well as at 16 months in the context of the process evaluation

Abbreviations: *APID* Appropriateness of Psychotropic Prescription In Dementia, *CMAI* Cohen–Mansfield Agitation Inventory, *CPS* Cognitive Performance Scale, *CVF* Competing Values Framework, *EBPAS* Evidence-Based Practice Attitude Scale, *MPT* Multidisciplinary project team, *NPS* neuropsychiatric symptoms, *NH* Nursing homes, *NPI-NH* Neuropsychiatric Inventory-Nursing Home, *QoL* Quality of Life, *RISE* Revised Index of Social Engagement, *VAS* Visual analog scale

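### Residents who leave are replaced by new admissions enrolled with the allocation known, so up to about one fifth of residents at month 8 could be selected differently in the two arms

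*Protocol article*

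**What the plan says.** Under Sample size, the protocol article states that "we can also anticipate a loss to follow-up of about 30% per year", "which would amount to 40% in the 16 months in our study". It makes no further allowance for this attrition, because "in the event a resident dies or moves away from the unit, we will enroll the newly admitted resident". It accepts one consequence: "Consequently, the case mix during our study will vary".

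Under Design and eligibility, homes are randomised to start the intervention at once or after 8 months, and "the NH staff and researchers will be aware of their participation group by design"; only the statistician is blinded. The deferred homes give usual care until month 8 and then start the intervention.

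Under Study population and recruitment, residents must "have a life expectancy of at least 3 months, as judged by a physician", have a dementia diagnosis and give written consent. For a resident who is not competent, the home's registry office posts the form to the legal representative. There is one reminder, and without a reply the resident is left out. Under The PAR-RCT study, every project team includes at least one physician.

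Under Data analysis, the primary comparison is between arms, adjusted for the baseline outcome, time and confounders such as cognition (CPS) and type of dementia.

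**The concern.** Randomising homes protects the comparison for residents who are identified independently of the allocation. Replacements are not: they are admitted, judged eligible and asked for consent while the home knows which condition it is in. If start homes take in more, fewer or different new residents than deferred homes, the arms drift apart in case mix for reasons unrelated to prescribing.

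The article foresees that case mix will change over time, but does not consider that it may change differently by arm. Under limitations it links selection bias to the voluntary participation of homes. Its general remark on lack of blinding does not reach the recruitment of residents after allocation. The comparison exposed is the one that matters most, because month 8 is the only follow-up measurement at which one arm is still on usual care.

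**Working it through.** **Inputs from the article.** Loss 30% per year; loss 40% over 16 months; two periods of 8 months; replacement by new admissions; target effect 5 APID points, SD 15; 364 drug users and 607 residents (all under Sample size or Design and eligibility).

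**Step 1: reproduce the plan's own figure.** Linear scaling gives 0.30 × 16/12 = 0.40, the stated 40%. A constant hazard would give 1 − 0.70^(16/12) = 37.8%. The article therefore scales linearly.

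**Step 2: the same rule at month 8.** Linear: 0.30 × 8/12 = 0.20. Constant hazard: 1 − 0.70^(8/12) = 0.212. If every departure is replaced, this is the share of month-8 residents enrolled after the start:
- of 364 drug users, 0.20 × 364 = 73 (77 with constant hazard);
- of 607 residents, 0.20 × 607 = 121 (128 with constant hazard).

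The drug-user count assumes the same loss in users and non-users.

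**Step 3: incomplete refilling.** Let f be the share lost and q the share of vacated places that yield a consenting resident (assumed; the article gives no value). The replacement share is f·q / (1 − f + f·q).

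| q | f = 0.20 | f = 0.212 |
|---|---|---|
| 0.50 | 0.10/0.90 = 11.1% | 11.9% |
| 0.75 | 0.15/0.95 = 15.8% | 16.8% |
| 1.00 | 20.0% | 21.2% |

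So 20% is close to a ceiling, and 11% to 17% covers partial refilling.

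**Step 4: possible shift in the month-8 contrast.** Each arm's mean is a mixture of original residents and replacements. If the replacements differ between arms by d points through selection alone, the unadjusted contrast moves by share × d. The article gives no value for d, so these are assumptions, shown at the 20% share:
- d = 3: 0.20 × 3 = 0.6 points, 12% of the 5-point target;
- d = 5 (0.33 SD): 1.0 point, 20%;
- d = 10 (0.67 SD): 2.0 points, 40%.

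At a share of 11.1%, d = 5 gives 0.111 × 5 = 0.56 points.

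**Step 5: does the planned adjustment remove it?** A resident admitted after the start has no month-0 APID value, and any first value is measured under the allocated condition. Adjusting for the baseline outcome therefore cannot correct for how that resident was selected. CPS and dementia type can be adjusted for, but cover only part of case mix.

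**The case against.** Several points on the other side are fair. The replacement sentence reads as a rule that takes in whoever is newly admitted, not as a choice by the home. For residents who are not competent, expected to be common, the registry office and not the physician sends the form, with a fixed reminder and a fixed rule for non-response. The process evaluation already covers recruitment and reach, and the limitations concede that awareness of the condition may bias results. The size of d is not anchored in any document, and a 10-point difference arising only from a life-expectancy check and consent would be large. How much weight replacements carry in the adjusted model is not known either, so the shift in the adjusted estimate could be smaller than in Step 4. These points limit the size of the concern. They leave a physician's judgement and a voluntary reply, both exercised with the allocation known.

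Three stronger readings are tempting and are not supported:
- A reader might infer from footnote c to Table 2 that the month-0 cohort was also enrolled with the allocation known. That footnote schedules two staff questionnaires, at month 0 in start homes and at month 8 in deferred homes. It says nothing about when residents consent or when APID data are extracted.
- A reader might count the competence judgement as a further filter. It decides who is asked to consent, not who is eligible.
- A reader might argue that the toolkit theme on involving relatives raises consent in start homes. The theme is one of eight that homes may draw on, and nothing connects it to returning consent forms.

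**Conclusion.** The concern holds as a recruitment risk created by a stated rule. Up to about 20% of residents at month 8 (about 11% to 17% with 50% to 75% refilling) would have entered with the allocation known, and the planned baseline adjustment cannot correct for their selection. The share rests on the article's 30% annual loss, scaled linearly as the article does, and on equal loss in drug users and non-users.

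The documents do not show that selection will differ by arm, and the resulting bias cannot be sized from them. The figure of up to 1 point is conditional on an assumed 5-point difference among replacements and applies to the unadjusted contrast. The trial remains viable and the sample-size arithmetic is not at issue. The precautions are worth taking because those at enrolment cannot be added after the data are in.

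**What to change.** 1. Approach every new admission with dementia on a participating unit for consent, by the same procedure and on the same dates in both arms. The existing registry-office mailing can serve as the base. Report by arm the numbers admitted, judged ineligible and not consenting; the process evaluation is a natural place.
2. Pre-specify a sensitivity analysis of the month-8 arm contrast restricted to residents enrolled at month 0, reported beside the analysis of all residents. No rule should switch the conclusion from one to the other once results are seen. State the caveat that effects may differ between existing and new residents for reasons other than selection, since a change in unit practice can act differently on established prescriptions and on new ones. Residents enrolled at month 0 may also be lost unequally by month 8.
3. Where feasible, complete the month-0 resident list and consents before homes are told their allocation.

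The cost is somewhat more record-keeping, one extra and less precise analysis, and possibly a short delay in telling homes their group. No extra homes are needed and the intervention does not change.

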### Data analysis

Primarily, we will examine results between both arms; the intervention group and the control group. Secondarily, we will examine results between the short intervention duration (8 months) and the long intervention duration (16 months). All data will be entered in a secured digital data management program. After collection, the data will be checked for outliers and extracted into a statistical software package. Descriptive statistics will be used to compare the baseline data between groups. A multilevel model will then be used to study the effects of a tailored intervention and implementation plan on reducing inappropriate psychotropic drug prescribing, based on the methods described by Twisk [73]. This model will be used for both the primary and secondary outcomes to account for the dependency of information due to the repeated measurements and cluster randomization. A restricted iterative generalized least squares algorithm will be used to estimate the regression coefficients, and the Wald test will be used to obtain a *P* value for each regression coefficient. Models will include a fixed and a random intercept.

Analyses will be adjusted for baseline outcome values (e.g., inappropriate psychotropic drug prescribing and NPS), time, and confounders (e.g., cognitive abilities, as measured with the CPS, type of dementia, distress in nurses due to NPS). We will adjust for factors that could explain why an intervention did not succeed at the team level (e.g., staff attitudes toward the use of new interventions or treatments, as measured by the EBPAS, and the cooperation between staff members, the working conditions and characteristics of the DSCU, as measured by the CVF scale). Possible interaction effects of the intervention with time and with an NH will also be investigated. Sensitivity analyses will be used to examine differences between NHs with respect to extent of performance, considering whether degree of implementation (such as more coaching) is associated with a greater reduction of inappropriate prescribing or whether attitude serves as an effect modifier. When indicated, subgroup analyses will be used to consider NHs that implement their plans unsuccessfully and NHs that implement their plans successfully. We will also conduct a missing value analysis to evaluate whether missing data are likely to be missing at random, and we will consider replacement if appropriate. Normal probability plots and plots of standardized residuals versus predicted values will be inspected to assess whether the assumptions of normality and homogeneity of variance are met. In the event of noncompliance, data transformation will be considered. The double ratings of QoL and health status, as perceived by nursing staff and family members, will be analyzed separately. Data from the process evaluation interviews will be examined in the content analysis and any barriers and facilitators will be analyzed according to the Consolidated Framework For Implementation Research [74].

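### The primary model's random part is given only as a random intercept, with no level named and no NH-by-period term, so its error rate holds only if nursing-home levels stay constant over 16 months

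*Protocol article*

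**What the plan says.** The Data analysis section plans one multilevel model for the primary and secondary outcomes. Its purpose is "to account for the dependency of information due to the repeated measurements and cluster randomization", so two sources of dependency are named. Estimation is by restricted iterative generalized least squares, and "the Wald test will be used to obtain a *P* value for each regression coefficient". The random part is then given as: "Models will include a fixed and a random intercept". The sentence does not say whether the intercept belongs to the NH, the resident or both, and it mentions no NH-by-period effect.

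The same section adds adjustment for baseline outcome, time and confounders, and will explore interactions of the intervention with time and with NH.

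The design has 16 NHs, 8 per sequence, with the primary outcome "based on data collected at baseline, 8 months, and 16 months". The Sample size section uses "5 points minimum (standard deviation = 15) on the APID index", an ICC of 0.1 and a design factor of 1.28. It expects about 40% of residents to be lost over 16 months and replaced by new admissions, with a shifting mix of residents as a result. Design and eligibility expects high turnover of residents and staff. The Discussion notes that every NH picks its own interventions.

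**The concern.** A random intercept, at whatever level, lets an NH differ from the others by a fixed amount. Apart from the common time effect, the NH's level is then assumed constant from baseline to 16 months. The protocol gives several reasons to expect otherwise: residents and staff change, the case mix moves, and each NH follows its own plan and may revise it after the 8-month feedback.

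A stepped-wedge estimate draws heavily on change within NHs. If an NH's level shifts between waves for reasons unrelated to the intervention, the shift enters the effect estimate. A model without an NH-by-period term attributes too little variance to it. At stake is the error rate of the primary P value and of every secondary comparison from the same model. The protocol speaks of P values, but any confidence interval rests on the same standard error (SE).

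**Working it through.** **The plan's own figure.** Unadjusted size per arm is 2 × (1.96 + 0.8416)² × 225 / 25 = 141.3, so 142, and 284 in total. The stepped-wedge design factor has 2 steps, 1 baseline wave, 1 wave per step, 25 residents per NH and ICC 0.1. It is [1 + 0.1(50 + 25 − 1)] / [1 + 0.1(25 + 25 − 1)] × 3(0.9) / (2 × 1.5) = (8.4 / 5.9) × 0.9 = 1.281. Then 284 × 1.281 = 364. The sample size reproduces and is not in dispute. It uses a single ICC with no decay over time, the same assumption as the model.

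**Inputs.**
- From the protocol: variance 15² = 225, ICC 0.1, 16 NHs, three waves, 364 / 16 ≈ 23 users per NH.
- Assumed: a correlation of 0.5 between measurements of one resident within an NH, and a correlation c of an NH's level between periods. c = 1 means no drift.
- Simplification: closed cohort (relaxed below).

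**True variance.** The NH variance is 0.1 × 225 = 22.5, of which 22.5c is constant and 22.5(1 − c) is NH-by-period. The within-NH variance is 202.5, half lasting and half occasional (101.25 each). Each half contributes 101.25 / 23 = 4.40 to an NH mean. The NH means then have

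- a part shared across waves, A = 22.5c + 4.40
- a part specific to one wave, B = 22.5(1 − c) + 4.40

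For sequences 0,1,1 and 0,0,1 with 8 NHs each and fixed period effects, the standard stepped-wedge variance reduces to Var = B(B + 3A) / (4B + 8A).

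- c = 1: A = 26.90, B = 4.40, Var = 1.61, SE = 1.27
- c = 0.9: A = 24.65, B = 6.65, Var = 2.40, SE = 1.55
- c = 0.8: A = 22.40, B = 8.90, Var = 3.15, SE = 1.78
- c = 0.6: A = 17.90, B = 13.40, Var = 4.57, SE = 2.14

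**What each reading reports.**
- NH + resident intercepts leave 22.5(1 − c) out of B, so the reported SE stays at 1.27 to 1.32 while the true SE rises to 2.18. At c = 0.8 it is 1.29 against 1.79, a ratio of 0.72.
- An NH-only intercept treats one resident's three measurements as three residents, so B is about 202.5 / 23 = 8.80 and the SE about 1.76 whatever c is. That is too large at c = 1. It matches the truth at c = 0.8 only by coincidence (true B = 8.90), and it is too small at c = 0.6.
- A resident-only intercept reports 1.22 to 1.27 against a true 1.39 to 2.14.

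Type I error is P(|Z| > 1.96 × reported SE / true SE), with variance components at their limiting values:

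| c | NH + resident | Resident only | NH only | NH + NH-by-period + resident |
|---|---|---|---|---|
| 1 | 5.0% | 8.6% | 0.7% | 5.0% |
| 0.9 | 10.5% | 13.6% | 2.6% | 5.0% |
| 0.8 | 15.6% | 17.9% | 5.1% | 5.0% |
| 0.6 | 23.6% | 24.7% | 10.6% | 5.0% |

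**Checks.** For NH + resident at c = 0.8, simulation gave 12.8% in a closed cohort (600 runs). It gave 17.1% in an open cohort of 25 with 5 replaced per period (350 runs). In the open cohort, with ICC 0.05–0.1, resident correlation 0.3–0.7 and c 0.6–0.9 (18 settings), the ratio of reported to true SE was:
- 0.51–0.93 for NH + resident, too narrow in all 18
- 0.51–0.83 for resident only, too narrow in all 18
- 0.75–1.31 for NH only: 7 too narrow, 2 about right, 9 too wide

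With the planned baseline adjustment, outcomes at 8 and 16 months, ICC 0.1 and resident correlation 0.5, type I error at c = 0.9, 0.8 and 0.6 was 8.2%, 11.5% and 17.3% for NH + resident. For NH only it was 4.7%, 6.9% and 11.6%.

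**The case against.** The article is condensed. It cites a published method for its model, and the levels of random effects are often left to a fuller document. Because the stated purpose covers both repeated measurements and clusters, one intercept per level is a natural reading. This stands in part. A reader might infer that the model cannot represent repeated residents at all; the text does not support that, since NH + resident intercepts handle them and are exactly valid without drift.

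A reader might also infer that the intervals are too narrow in most realistic cases. That rests on correlations the protocol never gives, and counting cells in a chosen grid does not show what is realistic. Under an NH-only intercept the error often goes the other way. Baseline adjustment also reduces the inflation, though it does not remove it.

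Third, a reader might treat the Wald test with 16 clusters as an error. The protocol states no normal reference distribution, and once NH-by-period is included, simulated Wald error is 3.4–6.3%. If the statistic followed t on 14 degrees of freedom, a 1.96 cut-off would give 7.0%. This is minor.

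The planned time adjustment removes only the common trend. The interaction analyses are exploratory and leave the stated random part as it is.

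**Conclusion.** The point holds in limited form. The article specifies the estimator, the test and the random part, and the stated random part contains no term for NH levels that change between waves. On the generous reading (NH + resident) the nominal 5% holds only without drift. It becomes about 10%, 13–17% and 24% at between-period correlations of 0.9, 0.8 and 0.6, with ICC 0.1 as stated and resident correlation 0.5 assumed. Baseline adjustment brings these to about 8%, 12% and 17%. On a single-intercept reading, resident-only is too narrow throughout, and NH-only runs from too wide to too narrow. The direction of the error therefore cannot be settled from the text. Severity is moderate: the gap concerns the primary analysis and is easily closed, but its size depends on quantities the protocol does not state.

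**What to change.** Replace the random-intercept sentence with one that names random intercepts for NH, NH-by-period and resident within NH, with period as a categorical fixed effect, for primary and secondary outcomes alike. With NH-by-period added, reported and true SE agree in every setting examined.

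The cost is a sentence or two of wording and standard software. If NH levels do not drift, little is lost: the SE is 1.27 with or without the term. If they do, intervals widen to reflect it, by a factor of 1.55 / 1.28 = 1.2 at c = 0.9, 1.78 / 1.29 = 1.4 at 0.8 and 2.14 / 1.32 = 1.6 at 0.6 (closed cohort, no baseline covariate). A small-sample t reference for 16 clusters is an optional refinement.
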